**Methods:**

The prospective, controlled before-and-after study is conducted in 3 phases (total duration: 24 months): preintervention, intervention, and postintervention analyses. The number of selected clusters (clinical centers) is limited to 4: one for each intervention, plus a cluster where no intervention is performed (control arm). The interventions are as follows: opening the facility on one Saturday per month only for men, defined as a *special day*; testing peer-to-peer counseling among men, *male champions*; and providing a noneconomic incentive to all women who are accompanied by their partners to the facility, *nudge*. The primary outcome of the study is to evaluate the differences in retention in care and adherence to therapeutic protocols among women; the intermediate outcome is the assessment of differences in male involvement. The level of male involvement in the health of their partners (intermediate outcome) will be evaluated through a dedicated questionnaire administered at baseline and in the postintervention phase. Data will be collected at the clinical centers and stored in 2 electronic databases managed using 2 different types of software.

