In the preintervention analysis, the baseline situation of the 3 participating centers will be evaluated. The aim of this phase is to set a starting point to weigh the relative effect of each intervention to be studied. For that purpose, baseline data of each study site will be collected. To evaluate the effect of the interventions, the same indicators will be measured during the pre- and postintervention phases, as described above. The preintervention phase will last 9 months. During this period, data will be collected at each site and included in a database.

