### Setting and Participants

The study was performed in Malawi within the Disease Relief through Excellent and Advanced Means (DREAM) program. DREAM is a health program managed by the Community of Sant’Egidio in 11 African countries [28]. The program delivers a number of health services: HIV care, HIV PMTCT, malnutrition prevention and control, care of noncommunicable diseases, tuberculosis diagnosis and treatment, cervical cancer screening, and treatment of early lesions [29-33]. The DREAM program in Malawi runs 13 health centers and 3 laboratories in collaboration with the Ministry of Health. Currently, the DREAM program in Malawi has cared for over 86,000 patients and assisted over 12,000 HIV-positive pregnant women in the prenatal care and delivery of HIV-uninfected babies. In addition, the DREAM program aims to address health inequalities related to HIV, along with barriers experienced by women in accessing services. For this purpose, an expert client model aimed at improving retention in care and facilitating the inclusion of social aspects in the clinical process was launched [34]. However, activities involving male partners with the goal of improving access of their partners to services have never been tested in this model.

Given the limited resources available for the study and the practical difficulties related to the disadvantaged context in which the study was conducted, sample size calculations and criteria for assigning interventions were based on a pragmatic approach. The number of selected clusters is limited to 4, one for each intervention plus a cluster where no intervention will be performed as a control arm. The number of participants enrolled for data collection is given by the number of patients attending the selected clinical centers during the pre- and postintervention phases. Therefore, the main unit of analysis of the study is the cluster, which is the clinical center. Thus, the interventions will target each health facility.

The following criteria were followed to select the 4 centers included in the intervention:

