### Data Collection and Storage

Data will be collected at the clinical centers and will be stored in 2 electronic databases managed through 2 different types of software:

Clinical and medical service data are routinely collected through an electronic DREAM program health record software used routinely at the clinical centers named DREAM_S [37].Data on health behaviors reported by patients who participate in the study will be collected through the software created specifically for the study, also respecting rules for patient privacy and data security.

In the preintervention phase, data will be collected at the medical visit immediately after the enrollment visit to evaluate the partner's acceptance of the invitation to come to the clinical center for testing and counseling in the company of the patient. In the postintervention phase, data will be collected 2 months from enrollment to allow for a wash-out period where the effects of the interventions would be expressed.

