### Outcomes and Statistical Methods

The outcomes will be divided into 2 levels: (1) evaluation of the variations in retention in care and women's adherence to therapeutic protocols (primary outcome) and (2) assessment of the variations in male involvement (intermediate outcome).

Retention in care and adherence to treatment protocols are primary outcomes. Retention in care will be measured as the cumulative proportion of dropouts from the treatment program at 6 months, 1 year, and 2 years (excluding patients transferred to another center or those who died). Adherence will be measured through the following indicators: (1) the cumulative proportion of medical appointments missed in a month in the center; (2) the cumulative proportion of appointments for drug delivery missed in a month in the center; (3) the cumulative proportion of women who suppressed viral load; and (4) the cumulative proportion of women with a suppressed viral load that has a rebound in viremia.

To evaluate the level of male involvement in the health of female partners (intermediate outcome), a dedicated questionnaire will be delivered to female partners at baseline (preintervention) and in the postintervention phase. The survey measures the following outcomes related to male involvement: (1) proportion of women accompanied by partners at the facility after receiving an invitation card; (2) proportion of men accepting HIV testing and counseling (if not yet received in the last 6 months); (3) level of partner involvement in the care process measured through a score scale based on health practices reported by the female partners; and (4) level of gender-based violence in the family measured through a score scale based on violent or negative practices reported by female partners.

Some indicators will be collected to monitor the delivery of the intervention and possibly evaluate correlations with the dose of delivery of the 3 interventions, as outlined in Textbox 1.

The primary and secondary indicators of effectiveness are the same for all interventions, hence making it possible to assess the differential impact of the community, health system, and structural-level interventions, particularly with respect to interventions based only on individual and interpersonal levels. These interventions will be compared with the usual services offered at the fourth center.

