## Results

The enrollment of patients in the preintervention phase started in July 2019 and ended on March 31, 2020. There is an ongoing analysis of preliminary data collected at the 4 centers during the preintervention phase. In total, 452 female participants were enrolled in the preintervention phase, with the following distribution: Namandanje (n=133); Kapeni (n=78); Kapire (n=75); and Balaka (n=166). Several meetings have been performed at the centers to organize the intervention phase. As of August 1, 2020, the interventions were initiated at the 3 centers and by September 2020 were ongoing.

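### The monthly adherence indicators have no effect contrast for the months when the interventions run, while 1- and 2-year retention of the baseline women runs into those months and blurs the before/after split.

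*Protocol article*

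**What the plan says.** The Protocol article (Strategy of the Study) lists three phases: preintervention, intervention and postintervention analyses. The Abstract gives 24 months in total, and Strategy of the Study gives 9 months for the preintervention phase.

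- **Where effect is measured.** Strategy of the Study: "the same indicators will be measured during the pre- and postintervention phases".
- **Who is counted.** Setting and Participants: the number enrolled for data collection is "given by the number of patients attending the selected clinical centers during the pre- and postintervention phases".
- **When postintervention data are taken.** Data Collection and Storage: "In the postintervention phase, data will be collected 2 months from enrollment to allow for a wash-out period". The sentence goes on to describe this as time for effects to be expressed.
- **What is collected on delivery.** Outcomes and Statistical Methods, with Textbox 1, lists counts of meetings, attendance, services and incentives.
- **Primary indicators.** The same section measures retention as cumulative dropout at 6 months, 1 year and 2 years. Adherence includes "the cumulative proportion of medical appointments missed in a month in the center", a matching indicator for drug delivery, and two viral load proportions. Retention is also to be analysed by Cox regression.
- **Data source.** Data Collection and Storage: "Clinical and medical service data are routinely collected through an electronic DREAM program health record software". This is not tied to a phase.
- **Dates.** Results: preintervention enrolment ran from July 2019 to 31 March 2020. "As of August 1, 2020, the interventions were initiated at the 3 centers".

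**The concern.** Two parts of the plan do not fit together.

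First, the monthly adherence indicators can be computed for any calendar month from a record that is filled routinely. Yet the text assigns effect measurement to the two outer phases and gives the intervention phase only delivery counts. The effect while the special days, champion meetings and incentives are running is then not estimated for these indicators. The Limitations section hopes for a strategy that can be implemented at other sites, so that effect is of direct interest. The plan also mentions possibly correlating outcomes with the dose of delivery, which is hard to do without outcome data from the months of delivery.

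Second, the retention horizons are long relative to the phases. If the women enrolled at baseline supply the before value for 1- and 2-year retention, part of their follow-up falls after the interventions began. At the three intervention centers, any benefit in that time is credited to baseline, which shrinks the before/after difference. At the control center there is no such exposure.

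**Working it through.** **Inputs.** Total duration 24 months (Abstract); preintervention 9 months (Strategy of the Study); enrolment July 2019 to 31 March 2020 and interventions under way as of 1 August 2020 (Results); retention at 6, 12 and 24 months (Outcomes and Statistical Methods).

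**Assumptions.** Month 0 is 1 July 2019. Interventions start on 1 August 2020; an earlier start would enlarge the overlaps below. Retention is counted from enrolment, because the article does not define time zero.

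**Step 1: reproduce the plan's figure.** July 2019 to the end of March 2020 is 9 months, as stated.

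**Step 2: place the intervention.** 1 July 2019 to 1 August 2020 is 13 months. That leaves 13 − 9 = 4 months (April to July 2020) between the end of baseline enrolment and the start, and 24 − 13 = 11 months for intervention plus postintervention if the 24-month total is kept. On the planned calendar without the gap, 24 − 9 = 15 months remain.

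**Step 3: exposed time in the baseline women's retention windows.** A woman enrolled at month e (0 to 9) with horizon h has max(0, e + h − 13) months after intervention start.

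| Horizon h | e = 0 | e = 9 | Share of window, e = 0 to e = 9 |
|---|---|---|---|
| 6 months | 0 | 9 + 6 − 13 = 2 | 0 to 2/6 = 33% |
| 12 months | 0 | 9 + 12 − 13 = 8 | 0 to 8/12 = 67% |
| 24 months | 0 + 24 − 13 = 11 | 9 + 24 − 13 = 20 | 11/24 = 46% to 20/24 = 83% |

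The 24-month row assumes each woman is followed for her full window. If follow-up ends at study month 24, the exposed part is 24 − 13 = 11 months for every woman, and only a woman enrolled at month 0 completes 2 years. At 12 months, exposure is zero only for e ≤ 1, that is, for women enrolled in the first month.

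**Step 4: the postintervention side.** The length L of the intervention phase is not stated in the text. For assumed L of 3, 6 or 9 months, the postintervention phase has at most 15 − L = 12, 9 or 6 months as planned, or 11 − L = 8, 5 or 2 months by the reported dates. A 1-year window from postintervention enrolment fits only on the planned calendar, with L of 3 months or less and enrolment at the very start of the phase. A 2-year window fits in neither outer phase.

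**Step 5: the monthly indicators.** They are defined per center and month and have no such horizon. For them the phase statement can be applied literally, and then the L intervention months carry no effect contrast. The text assigns no other contrast to those months.

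**The case against.** The case against is substantial. Comparing before with after is what a controlled before-and-after study does, and the text never says that intervention months are excluded. Extraction windows are often left to a fuller document, and the figure showing the study structure, which may give the phase lengths, is not available here.

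A reader might infer that the intervention months are left out of all the primary outcomes, so that the study estimates only what remains afterwards. The documents do not support that. Retention at 1 and 2 years, counted from enrolment, runs through those months. No section says that the interventions stop before postintervention measurement. The 2-month interval is counted from enrolment and is described as time for effects to be expressed, not to fade. The parallel sentence for the preintervention phase concerns the partner's response to the invitation, so this timing may govern the questionnaire data rather than the health record.

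A reader might also want to put a power loss on the omitted months. That needs assumed phase lengths, assumed rates of fading, full effect from the first day and independent months. With one center per arm, variation between center and period does not shrink as months are added, so such figures would not be reliable.

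Two things stand after this. The stated phases give the monthly indicators no contrast during the interventions, and the retention horizons cannot be kept within the stated phases. The second is a conflict within the article, not a detail left to another document.

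**Conclusion.** The point holds in limited form. The monthly missed-appointment and missed-pickup indicators have no planned effect contrast for the intervention months, although the data are routinely recorded. For retention, the before/after split and the horizons conflict: among women enrolled at baseline, at least 46% of a 2-year window, and up to 67% of a 1-year window, lies after the interventions began. These are shares of time, not of effect, and they rest on counting from enrolment, on month 0 being 1 July 2019 and on a start on 1 August 2020. The direction of the retention problem is toward a smaller before/after difference if an intervention works. Its size, and the precision or power gained by using the intervention months, cannot be derived from the document. This is worth changing before analysis; it does not invalidate the design.

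**What to change.** 1. In Strategy of the Study and Data Collection and Storage, state that the record-based primary indicators (missed medical appointments, missed drug pickups, dropout, viral load) will be extracted from the routine health record by calendar month at all four centers, from July 2019 to study end.
2. Label every month by phase, including April to July 2020, and state the start and end of each phase and whether delivery continues into the postintervention phase.
3. Add an intervention-phase versus preintervention contrast, relative to the control center, with a short start-up lag fixed in advance. Report it alongside the planned postintervention contrast. It need not become the main one, since that would change the estimand and is a matter for the investigators.
4. Define time zero for retention and split person-time at intervention start (for example, as a time-varying exposure in the planned Cox model), so that exposed time is not counted as baseline.
5. Reconcile the phase statement and the 2-month interval with the 6-month, 1-year and 2-year horizons, saying which horizons each group of women can supply within 24 months.
6. Leave the questionnaire outcomes at their two time points.

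The cost is wording, a further extraction from an existing record, extra analysis and one more contrast to report. It needs no new visits or patients. Early intervention months may dilute the added contrast, which is the reason for the lag.

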**Figure 2 figure2:**
[figure not shown]
General structure of the study.

### Setting and Participants

The study was performed in Malawi within the Disease Relief through Excellent and Advanced Means (DREAM) program. DREAM is a health program managed by the Community of Sant’Egidio in 11 African countries [28]. The program delivers a number of health services: HIV care, HIV PMTCT, malnutrition prevention and control, care of noncommunicable diseases, tuberculosis diagnosis and treatment, cervical cancer screening, and treatment of early lesions [29-33]. The DREAM program in Malawi runs 13 health centers and 3 laboratories in collaboration with the Ministry of Health. Currently, the DREAM program in Malawi has cared for over 86,000 patients and assisted over 12,000 HIV-positive pregnant women in the prenatal care and delivery of HIV-uninfected babies. In addition, the DREAM program aims to address health inequalities related to HIV, along with barriers experienced by women in accessing services. For this purpose, an expert client model aimed at improving retention in care and facilitating the inclusion of social aspects in the clinical process was launched [34]. However, activities involving male partners with the goal of improving access of their partners to services have never been tested in this model.

Given the limited resources available for the study and the practical difficulties related to the disadvantaged context in which the study was conducted, sample size calculations and criteria for assigning interventions were based on a pragmatic approach. The number of selected clusters is limited to 4, one for each intervention plus a cluster where no intervention will be performed as a control arm. The number of participants enrolled for data collection is given by the number of patients attending the selected clinical centers during the pre- and postintervention phases. Therefore, the main unit of analysis of the study is the cluster, which is the clinical center. Thus, the interventions will target each health facility.

The following criteria were followed to select the 4 centers included in the intervention:

The centers represented the Malawian population. As Malawi is a country where 83% of the population resides in rural or semirural environments [35], rural clinics were selected.Centers that only provided maternal services were excluded because it was not possible to use a male-friendly approach in a center that is designed to accommodate only women.The remaining centers with the highest number of female patients were selected.

The *special day* intervention was assigned to the center of Balaka (Balaka district). At this site, health care staff are available to offer the planned services. The *male champion* intervention was assigned to the Kapire center (Machinga district), where there are patients available to engage themselves as male champions who have sufficient levels of education necessary to perform the task assigned to them and communicate with the researchers. The *nudge* intervention was assigned to the Kapeni center (Blantyre district), where the number of women being treated was consistent with the available budget necessary for the provision of noneconomic incentives.

Although the unit of analysis is the clinical center, and therefore all patients who are referred, the study focuses on the population of adult females and the influence of male partners on the health practices of women. Therefore, data will be collected from this specific population. Eligibility criteria for women included the following: being HIV positive; inclusion in an HIV/AIDS prevention and treatment program; aged 18 years or older; and living at home with a male partner.

There are several possible criteria for defining a partnership relationship. In the Malawian context, the concept of marriage is understood in many different ways depending on local tradition or different religious practices [36]. Furthermore, mobility is quite high and there are situations in which the married partner spends longer periods away from the family or abroad; therefore, there is no possibility of directly influencing his wife's health practices. Hence, in this study, it was decided to consider the man who resides in the same house with the woman as a partner, regardless of religious or legal bonds between the two.

The enrollment of participants will be consecutively based on the order of patient appointments. Recruitment will be entrusted to doctors and clinical officers responsible for the medical visits of women participating in HIV treatment programs, who interact with patients during every visit to the clinical center. All women who met the eligibility criteria and agreed to participate in the study will be enrolled. Recruitment will be conducted before the medical examination: the software used for patient management reports to the clinician whether patients aged less than 18 years are enrolled, allowing the clinician to check entry criteria and invite eligible participants for study participation with the provision of informed consent.

### Data Collection and Storage

Data will be collected at the clinical centers and will be stored in 2 electronic databases managed through 2 different types of software:

Clinical and medical service data are routinely collected through an electronic DREAM program health record software used routinely at the clinical centers named DREAM_S [37].Data on health behaviors reported by patients who participate in the study will be collected through the software created specifically for the study, also respecting rules for patient privacy and data security.

In the preintervention phase, data will be collected at the medical visit immediately after the enrollment visit to evaluate the partner's acceptance of the invitation to come to the clinical center for testing and counseling in the company of the patient. In the postintervention phase, data will be collected 2 months from enrollment to allow for a wash-out period where the effects of the interventions would be expressed.

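### The visit-based male-involvement outcomes are measured at the next visit before the intervention but at 2 months after it, so the before-after contrast mixes intervention effect with a change of measurement window

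*Protocol article*

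**What the plan says.** Data Collection and Storage gives two timing rules in consecutive sentences.

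- Before: "In the preintervention phase, data will be collected at the medical visit immediately after the enrollment visit". The stated purpose is "to evaluate the partner's acceptance of the invitation to come to the clinical center for testing and counseling in the company of the patient". No number of days or weeks is given.
- After: "In the postintervention phase, data will be collected 2 months from enrollment to allow for a wash-out period". The interval is meant as a period "where the effects of the interventions would be expressed".

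Strategy of the Study rests the evaluation on comparability: "the same indicators will be measured during the pre- and postintervention phases".

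Outcomes and Statistical Methods lists, among the intermediate outcomes, the "proportion of women accompanied by partners at the facility after receiving an invitation card" and the share of men who accept HIV testing and counseling. Neither has a response window that would align the phases. The same section compares the three interventions with usual services at the fourth center. Its tests are the unpaired t, chi-square, Mann-Whitney and Kruskal-Wallis tests, with logistic and Cox regression; no contrast of phase by center is named.

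**The concern.** A before-after comparison needs the outcome observed over the same span in both phases. Here the partner has until the woman's next visit to respond in one phase and a fixed 2 months in the other. Accompaniment and test acceptance depend on how much time, or how many visits, the partner has. The phase with the longer window can therefore score higher with no intervention effect at all.

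The reason given for the 2 months makes the asymmetry plain: time is allowed for effects to appear, and baseline gets no matching allowance. That is a lag. A wash-out would be time for an earlier effect to fade.

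What is at stake is the reading of the intermediate outcome. Every intervention is meant to act on the women's outcomes through male involvement, so a spurious rise or fall there would mislead about which intervention engaged the partners.

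**Working it through.** The plan gives no figure for this point, so there is none to reproduce. The calculations below are illustrations.

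**Inputs from the article.** Baseline is measured at the next visit (interval not stated) and follow-up at 2 months (Data Collection and Storage). The significance level is .04 (Outcomes and Statistical Methods). Preintervention enrollment was 75 at Kapire, 78 at Kapeni, 166 at Balaka and 133 at Namandanje, total 452 (Results). Reported male involvement in Malawi ranges from 3.2% to 23% (Design of the Study and Theoretical Framework).

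**Assumptions.** A constant monthly chance h that a partner responds, accruing continuously; no intervention effect; next visit at 1, 2 or 3 months.

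**Step 1. Proportion responding by month m: 1 - (1 - h)^m.**

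- h = 0.15: 1 month 0.150; 2 months 1 - 0.85² = 0.2775; 3 months 1 - 0.85³ = 0.3859.
- h = 0.05: 1 month 0.050; 2 months 1 - 0.95² = 0.0975; 3 months 1 - 0.95³ = 0.1426.

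**Step 2. Artifact = value at 2 months minus value at the next visit.**

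| Next visit at | h = 0.15 | h = 0.05 |
|---|---|---|
| 1 month | 27.75 - 15.0 = +12.8 points | 9.75 - 5.0 = +4.8 points |
| 2 months | 0 | 0 |
| 3 months | 27.75 - 38.59 = -10.8 points | 9.75 - 14.26 = -4.5 points |

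**Step 3. What this could do to a simple before-after test.** Take the article's 3.2% and 23% as illustrative baseline proportions p at the next visit. If that visit is at m months, the 2-month value is 1 - (1 - p)^(2/m).

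- Visit at 1 month: 3.2% becomes 1 - 0.968² = 6.3%; 23% becomes 1 - 0.77² = 40.7%.
- Visit at 2 months: no change.
- Visit at 3 months: 23% becomes 1 - 0.77^(2/3) = 16.0%.

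For the 1-month case, a two-sided comparison of two independent proportions at .04, with postintervention numbers assumed equal to preintervention numbers, gives these chances of a false difference:

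| Center | p = 3.2% | p = 23% |
|---|---|---|
| Kapire (n = 75) | about 12% | about 61% |
| Balaka (n = 166) | about 23% | about 92% |

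With one common window, the timing artifact is zero and the rate returns to the nominal 4%.

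**Step 4. How much the control center would remove.** Suppose two centers share 1-month visit spacing but have h = 0.15 and h = 0.05.

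- Risk-difference scale: 12.75 - 4.75 = 8.0 points remain.
- Odds-ratio scale: the shifts are (0.2775/0.7225)/(0.15/0.85) = 2.18 and (0.0975/0.9025)/(0.05/0.95) = 2.05, a ratio of about 1.06.
- Complementary log-log scale: both shifts equal log 2 and cancel.

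If visit spacing differs between centers, the shifts differ on every scale. At h = 0.15, spacing of 1 month in one center and 3 months in another gives +12.8 against -10.8 points.

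**The case against.** The strongest reply has four parts.

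**Scope.** A reader might infer that all outcome data, including the primary outcome, are affected. The article does not support that: "Retention in care will be measured as the cumulative proportion of dropouts from the treatment program at 6 months, 1 year, and 2 years". Missed appointments are counted per month, and clinical data come from the routine electronic record. Nor should the point be extended to "the cumulative proportion of women who suppressed viral load" or to viral rebound. Nothing shows that the two timing rules govern those indicators, and a rebound proportion need not rise with time, because its denominator grows as more women become suppressed. The involvement and violence scores are reported levels, not shown to accrue with time. All of this stands, and the point is confined accordingly.

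**Size.** The visit interval and the monthly rates are assumed, and the artifact vanishes if visits are about 2 months apart. Accompaniment can happen only when the woman attends, so continuous accrual is a simplification; one visit in each window would mean one opportunity in each phase. This stands as a limit on magnitude. It does not remove the difference between the two rules.

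**Control.** The design is controlled, and no center is exempted from the timing rules. A shift common to all centers would largely cancel, and on a suitable scale equal baseline rates are not required. This also stands, but it needs equal visit spacing and a contrast of phase by center, and the article states neither.

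**Terminology.** Calling the lag a wash-out is an editorial fault, since the purpose is stated openly. Agreed; it is corrected in passing.

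**Conclusion.** The point holds for the visit-based male-involvement outcomes, chiefly accompaniment after the invitation card and partner acceptance of HIV testing. Followed as written, the plan confounds timing with phase for these indicators.

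That the windows are defined differently is certain from the text. The size and sign of the resulting bias are not: under the assumed rates of 5% and 15% a month they run from about -11 to +13 points, with zero in between. They rest on a constant response rate, continuous accrual and a next visit somewhere from 1 to 3 months. The control center reduces the problem to the part of the shift that differs between centers, provided the analysis actually uses it that way.

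**What to change.** Baseline has already been collected: preintervention enrollment closed on March 31, 2020. The common rule should therefore be the one already used.

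- In the postintervention phase, at all four centers, record these indicators at the first medical visit after enrollment and invitation.
- Record the enrollment-to-visit interval in both phases, so that spacing can be compared across phases and centers.
- Make that common time point the basis of the before-after comparison against control, and state the phase-by-center contrast.
- Keep the 2-month measurement as a secondary, lagged measure, and call it a lag.
- Re-derive baseline to day 60 only as a sensitivity analysis, and only where dated records of partner attendance and testing exist. The article does not show that they do, and the approach fails where visits are more than 60 days apart.

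The cost is protocol wording and one extra recording at a routine visit. The downside is that the main time point for these indicators may leave less time for effects to appear; the retained 2-month measure addresses that. The interventions began only in August 2020, so on the article's account the change can still be made before postintervention measurement.
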